### Intervention

An evidence-based smoking cessation intervention package was devised in order to represent a practical and replicable smoking cessation service in the primary health care setting of a developing country. The other arm of the randomized control trial represents the conventional smoking cessation service used in Thailand (Table 1).

**Table 1 T1:** Timetable of interventions in the randomized controlled trial and additional non-randomized arm of the ESCAPE study

		**Intervention**											
Visit number	1	2	3	4	5	6	7	8	9	10	11	12	13
Month	0	1	2	3	4	5	6	7	8	9	10	11	12
**New package service**													
Assertive communication	x	x	x	x									
Nicotine replacement chewing gum to those indicating need	±	±	±	±	±	±	±						
Family member assistance	x	x	x	x	x	x	x	x	x	x	x	x	x
Smokerlyzer as motivational tool		x	x	x									
**Existing service**													
Health care worker counseling patient at enrollment	x												
Routine 5 A service including assessment of nicotine dependence questionnaires	x												
Advice and encouragement on NCD clinic follow-up visits	x						x						x
**Refusing to give up smoking**													
Recruitment	x												

± shows the intervention to those who have indicated a need for nicotine replacement therapy.

#### New evidence-based service (intervention arm)

The new evidence-based service package arm will comprise the following interventions [14]: (1) during the first meeting, a primary care unit (PCU) nurse will motivate the patient to give up smoking by providing a clear explanation, and the same nurse will provide repeated advice each month for the next 3 months; (2) a piCO ^+^ smokerlyzer will be used to show the level of carbon monoxide (CO) the patient breathes out and the improvement of the patient’s lung health over 3 successive months; (3) a PCU nurse will train one member of the patient’s family on how to care for the patient until he/she has successfully given up smoking; (4) patients who suffer from nicotine craving are given nicotine replacement chewing gum.

#### The existing service arm (control arm of the randomized control trial)

The routine health service smoking cessation package will include the following: (1) during the first meeting the hospital healthcare worker advises the patient on how to stop smoking; (2) the patient answers questions about their smoking habit to indicate their level of nicotine dependency; (3) the patient is reminded by the healthcare worker on subsequent visits to the hospital how to stop smoking; (4) the patient is asked to let the healthcare worker know if and when he/she has successfully been able to give up smoking.

#### Difference between two service arms

The two service arms differ in several components (Table 1). In the new service arm, nursing intervention is an assertive communication between a patient and nurse to achieve the goal of stopping smoking rather than conventional patient counseling by the nurse or any health care staff as would be the case for routine arm group [16]. The PCU nurse will ask the patient what he/she knows about the risks of smoking and will provide education about them. Then an assertive form of communication will be established between the nurse and patient assisting in the patient’s attempt to give up smoking. The same PCU nurse will sustain such communication, along with the implementation of an action plan, for a period of 3 months after enrollment. This communication may include phone calls to the participant and his/her family.

Second, participants in the new service arm group will be able to see both the level of their nicotine dependence, via the colored diode light in the smokerlyzer breath analysis, and also the level of CO in their expired air, as compared to their questionnaire rating as would be the case for the routine arm group. This will provide both visible positive feedback and an achievable goal in the assertive communication between the nurse and patient.

Third, the most striking difference between the two service packages is the assigning, in the new service arm, of a family member to monitor, remind and motivate the smoker until smoking cessation is successful. The family member, trained by the PCU nurse, will be empowered by using an attractive “quit-smoking diary” along with three different colored stickers to record the participant’s choice on smoking each day: smoking (red), NRT chewing gum (blue) and non-smoking (white) (Figure 2). This diary is expected to serve as a reminder to both the smoker and the assisting family member.

**Figure 2 F2:**
[figure not shown]
A record book in which the family member will record a smokers’ progress of smoking cessation.

Fourth, nicotine replacement chewing gum will be included as one of the components in the new intervention arm. Participants in this arm will receive NRT when they have nicotine withdrawal symptoms [17,18]. A protocol for the provision of NRT has been developed based on Thailand’s Clinical Practice Guideline in Smoking Cessation [19]. NRT will be provided after screening for withdrawal symptoms [17], confirmed by the Fagerstrom test, or breath analysis by smokelyzer or Nicodep test, but only to those willing to use NRT [18,20]. Due to these differences between the two intervention arms, contamination between the two arms is expected to be low.

#### Non-randomized arm (refused to quit smoking)

Once participants have agreed and consented to participate in the trial, they will be asked whether they are willing to attempt to give up smoking (Figure 1). If the participant agrees to give up smoking, he/she will be randomized into the evidence-based new service package arm or the routine service package arm (Figure 1, Table 1). If the participant refuses to attempt to give up smoking, he/she will be automatically allocated to the non-randomized arm. Participants in this arm will not receive any active intervention for smoking cessation, apart from the routine medical service for their existing disease, such as diabetes and hypertension, provided under the universal coverage system.

#### Duration of interventions

The duration of the new smoking cessation service package is as follows:

1. Persistent motivation and coaching by a designated PCU nurse for a period of 3 months.

2. Monthly application of the piCO ^+^ smokerlyzer for a period of 3 months.

3. Assistance by a trained family member (or health care worker in cases of smokers living alone) for a period of 12 months.

The duration of the routine smoking cessation service package is as follows:

1. Counseling of the patient by a healthcare worker during only the first meeting at the NCD clinic of the PCU.

2. Reminding the smoker to stop smoking ad libitum on successive visits for a period of 12 months. The components of each service arm are shown in Table 1.

### Manual and training

An operational manual for the smokerlyzer will be prepared and provided to the study site PCUs. PCU nurses will be trained in how to use smokerlyzers 2 months prior to implementation. Details of the existing smoking cessation service will be reviewed and structured so as to represent the routine service arm in the study. A protocol for nicotine replacement chewing gum will be prepared by the team of researchers, director of Maetha Hospital, physicians, nurses and pharmacists [19]. The indications for NRT will follow the current guidelines for Thailand.

### Definitions

#### Smoking cessation

Smoking cessation is defined as the stopping of smoking for a period of at least 6 months and confirmed by the assessment of carbon monoxide (CO) in the smoker’s expired air using a smokerlyzer.

#### Diabetes

Diabetes mellitus is defined as one of the following criteria: HbA1C concentration of more than 6.5%, or fasting blood glucose of more than 126 mg/dL at least twice, or on the spot blood glucose level of more than 200 mg/dL at least once, simultaneously with 2-h post-prandial blood glucose of more than 200 mg/dL or a history of taking oral hypoglycemic drugs.

#### Hypertension

Hypertension is defined as **(1)** a systolic blood pressure (SBP) of ≥140 mmHg or a diastolic blood pressure (DBP) of ≥90 mmHg in participants who are not taking antihypertensive medication or **(2)** subjects who are taking medication for hypertension.

#### Cardiovascular disease (CVD) events

Myocardial infarction, coronary insufficiency, unstable angina, ischemic stroke, hemorrhagic stroke, transient ischemic attack (TIA), peripheral artery disease or heart failure will be counted as CVD events in this study. Patients with a known diagnosis of CVD will be screened and excluded.

#### CVD mortality

This is defined as any documented death caused by CVD during the study period.

### Study outcome and outcome measurements

#### Primary outcome

The primary outcome of the study is the smoking cessation rate at the 1-year follow-up, proven by measurement of carbon monoxide in parts per million (ppmCO).

#### Secondary outcomes

Secondary outcomes of the trial are:

1. Smoking cessation rate at the 6-month follow-up, proven by measurement of (ppmCO).

2. CVD risk measured by the Framingham general cardiovascular risk score at the 12-month follow-up.

3. Blood pressure and heart rate measured at the 6- and 12-month follow-up.

4. Number of CVD events and deaths at the 12-month follow-up.

5. Cost-effectiveness of the health service packages at the 12-month follow-up.

### Outcome measurements

#### Smoking cessation

This would be assessed by self-reported quitting confirmed by breath analysis of the level of carbon monoxide (CO) in expired air. A piCO ^+^ Smokerlyzer® [21] carbon monoxide monitor will be used for this assessment on the first visit, and again on the 6- and 12-month visits. It is a clinically proven way to determine the carbon monoxide level and easy to use in primary care. In previous studies, the Smokelyzer has been shown to have positive, predictive values for detecting smoking, at more than 95% [12,22]. It can also serve as a motivational tool for giving up smoking. Nicotine dependence will be assessed by the Fagerstrom Nicotine Dependence Test and the Nicodep Test [18,20]. The self-reported smoking cessation rate is ascertained by asking participants the number of cigarettes smoked in the preceding 24 h.

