### Study objectives

The primary objective is to compare the smoking cessation rate between a new evidence-based smoking cessation service package and the conventional 5 A approach to smoking cessation at the 1-year follow-up.

 The secondary objectives are:

1. to compare the smoking cessation rate at the 6-month follow-up.

2. to compare the CVD risk by Framingham general cardiovascular risk score among intervention and control groups at the 1-year follow-up.

3. to determine the characteristics of those who have successfully given up smoking and the determinants of behavioral change.

4. to determine the characteristics of relapse smokers after 6 months of cessation and the determinants of behavioral change.

5. to compare the cardiovascular disease events between ex-smokers, reduced smokers and continuous smokers at the 1-year follow-up.

6. to determine the cost-effectiveness of the new smoking cessation service package.

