	**Follow-up**												
Visit number	1	2	3	4	5	6	7	8	9	10	11	12	13
Month	0	1	2	3	4	5	6	7	8	9	10	11	12
Inclusion and exclusion criteria	x												
Framingham scoring	x						x						x
Self-reported smoking cessation	x			x			x						x
Smokerlyzer	x						x						x
Fagerstrom Test	x						x						x
Blood pressure	x	x	x	x			x			x			x
BMI	x			x			x						x
Blood glucose	x						x						x
Waist circumference	x						x						x
Hip circumference	x						x						x
HbA1C	x												
Lipid profile	x												
CVD event	x						x						x
CVD death	x						x						x
Questionnaires													
Demography	x												
Questionnaire assessing motivation to stop smoking (MTSS)	x						x						x
Questionnaire assessing cost effectiveness	x						x						x
Questionnaire assessing family support on smoking cessation	x						x						x
Questionnaire assessing health literacy	x						x						x

Moreover, the intervention design is an add-on design in which additional evidence-based components are added to the existing routine service [30]. Regarding the outcome measurement, most of the secondary outcomes are feasible to measure via the routine data collection of the study site hospital network. Furthermore, the sample size has been increased by 20% to compensate for dropouts.

The study is carefully designed randomized controlled trial, evaluating two approaches of active intervention and comparing the rate of behavior change. However, the CVD outcome event rate of the active intervention arms will also be analyzed and compared with that of the non-randomized arm made up of smokers refusing to try to give up smoking. It will require the adjustment of minimal residual confounders. Moreover, there will be different models of covariates used to analyze different outcomes. For instance, adjustments in the comparison of CVD events and deaths between the intervention and control arms may include family history, lifestyle, physical activity, alcohol consumption, dietary habits, current medications and socioeconomic status [25]. To assess physical activity as a covariate, a rapid physical activity assessment scale will be applied [31]. Therefore, possible confounders are collected and will be adjusted appropriately in later analysis [32] (Table 3).

**Table 3 T3:** Confounder measurements

**Confounder**	**Variables**	**How to measure**
Demographic characteristics	Age, sex, social status, family size, educational attainment, occupational history, income	Questionnaire

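### Smoking cessation is defined as at least 6 months without smoking but ascertained over the preceding 24 hours, so the primary outcome as measured is not the one defined

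*Protocol article*

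**What the plan says.** All references are to the protocol article.

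- **Definition** (Definitions, Smoking cessation): "Smoking cessation is defined as the stopping of smoking for a period of at least 6 months", with confirmation by expired CO.
- **Primary outcome** (Primary outcome): "The primary outcome of the study is the smoking cessation rate at the 1-year follow-up, proven by measurement of carbon monoxide". No duration is restated, so the definition above supplies it.
- **Measurement** (Outcome measurements, Smoking cessation): "This would be assessed by self-reported quitting confirmed by breath analysis of the level of carbon monoxide (CO) in expired air". The self-report part is then specified: "The self-reported smoking cessation rate is ascertained by asking participants the number of cigarettes smoked in the preceding 24 h".
- **Timing**: the "carbon monoxide monitor will be used for this assessment on the first visit, and again on the 6- and 12-month visits". In Table 2, the row "Self-reported smoking cessation" is marked at months 0, 3, 6 and 12, with nothing between 6 and 12.
- **Month-6 outcome** (Secondary outcomes): the CO-proven cessation rate at 6 months, using the same term and giving no separate definition.
- **Analysis** (Analyses plan; Smoking cessation rate): the Smokerlyzer-confirmed rate is compared between arms at 6 and at 12 months by chi-square, with relative risk and number needed to treat. No duration rule is added.

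**The concern.** The definition and the measurement describe different endpoints. One is sustained abstinence over half a year. The other is abstinence on the day before the visit, supported by a breath test at that visit. A participant who smoked through most of months 6 to 12 but not in the last 24 hours could be classed as having stopped for 6 months, provided the CO reading agreed.

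The primary comparison, the relative risk, the number needed to treat and the cost per additional percentage of quitters all depend on this classification. The 9% and 24% planning rates carry no abstinence definition either, so the design does not show which endpoint the trial was sized for. If both rules stay in the text, the choice between them may be made after the data have been seen.

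**Working it through.** **1. Does any section bridge the two rules?**

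| Possible bridge | Where | Does it supply a 6-month rule? |
|---|---|---|
| 24-hour question at month 12 | Outcome measurements, Smoking cessation | No. It covers 1 day of about 183 (365/2). |
| Same question at month 6 as well | Table 2 | No. It covers 2 days at most, and no section requires success at both visits. |
| CO at months 6 and 12 | Outcome measurements; Table 2 | No. These are two single readings that are not combined into a rule. |
| Questionnaires at months 6 and 12 on lifestyle and health behaviors | CVD events and death | Not tied to the cessation outcome. |
| Daily sticker diary | Difference between two service arms | Kept in the new-service arm only and not named as an outcome source. Using it would make ascertainment differ by arm. |
| Analysis rules | Analyses plan | None added. |

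Nothing asks for a quit date or for smoking since the previous visit.

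**2. Month 6 if the 6-month definition governs.** Participants are current smokers at month 0. To have 6 months of abstinence at month 6, they must stop at month 0. Someone who stops at month 1, 2 or 3, during the coaching in Table 1, has 5, 4 or 3 months by then and counts as a failure. If the 24-hour question governs, this problem disappears. The two consequences are alternatives and do not add up.

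**3. The plan's own sample size.** Inputs from Sample size: 9% vs 24%, 80% power, 95% confidence (taken as two-sided 0.05), 20% added, 164 per arm. The pooled two-proportion formula gives 95 per arm, or 108 with continuity correction. Multiplied by 1.2, these become 114 and 130. The stated 164 is not reproduced at 80% power. It is larger than needed, which is a separate matter and does not affect this point.

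**4. Illustration of the stricter definition.** Assumption, not in the article: 9% and 24% are 24-hour rates, and the same share *s* of quitters in each arm meets the 6-month rule.

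Power = Φ[(d − 1.96·SE0)/SE1], where d = p2 − p1, SE0 = √(2·p̄(1−p̄)/n) and SE1 = √((p1(1−p1)+p2(1−p2))/n).

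Example, s = 0.8, n = 131 (164 × 0.8): p1 = 0.072, p2 = 0.192, p̄ = 0.132, SE0 = 0.0418, SE1 = 0.0412. Then (0.120 − 1.96 × 0.0418)/0.0412 ≈ 0.92, and Φ ≈ 0.82.

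| s | Rates | Difference | NNT (1/d) | Power, 131 per arm | Power, 164 per arm |
|---|---|---|---|---|---|
| 1.0 | 9.0% vs 24.0% | 15 points | 6.7 | 91% | 96% |
| 0.8 | 7.2% vs 19.2% | 12 points | 8.3 | 82% | 90% |
| 0.6 | 5.4% vs 14.4% | 9 points | 11.1 | 69% | 78% |

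With an equal share in both arms the relative risk stays at 24/9 = 2.67, while the absolute difference and the number needed to treat change. If the share differs between arms, the relative risk changes too.

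**The case against.** The strongest reply is that the trial has more than one snapshot. CO is read at months 6 and 12, self-report is also taken at month 3, and a journal article may condense a fuller case record form. This holds in part. The material for a sustained-abstinence outcome is largely scheduled, and a fuller form is not excluded. But the article states both rules and they differ, so this is not detail left to another document. Analysis alone cannot recover six months of abstinence from a 24-hour question.

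A reader might also infer three stronger points that the document does not support.

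- **Objective 4** ("to determine the characteristics of relapse smokers after 6 months of cessation") might seem to apply only to people who stopped at enrollment. It does not. Someone who stops at month 1, 2 or 3 completes 6 months at month 7, 8 or 9 and can relapse before month 12.
- **The month-6 comparison** might seem unable to show an effect of the package. That is too strong. The restriction arises only under the 6-month definition. Even then, only people who agree to attempt quitting are randomized, so stopping at enrollment is plausible and coaching could help sustain it.
- **Loss of power** might be argued from short-term abstainers adding 5 or 10 points to both arms (14% vs 29%, 19% vs 34%). Power at 131 per arm would then fall from 91% to 84% or 79%. Those increments have no basis in the article. With 137 per arm, the base implied by 164/1.2, the figures are 92%, 86% and 81%, so power stays above the planned 80%.

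**Conclusion.** The contradiction stands. As written, the primary outcome is defined as at least 6 months of abstinence and measured as 24-hour abstinence with CO at the visit. The main harm is to the meaning of the result, which would be presented as 6-month cessation without having been measured as such. The month-6 problem is real but conditional on the 6-month definition governing.

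No numerical size follows from the article alone. The power figures of 82% and 69% (131 per arm) or 90% and 78% (164 per arm) rest on the assumed 80% and 60% shares, equal in both arms, and on 9% and 24% being 24-hour rates. They show what the stricter definition might cost in power. They are not evidence that the trial is underpowered.

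**What to change.** State one definition per time point and ask it identically in both arms.

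- **Primary outcome, month 12:** ask about smoking since the month-6 visit. Require self-reported abstinence over that period, with CO confirmation at both month 6 and month 12. Both readings are already in Table 2.
- **Month-6 secondary outcome:** give it its own point-prevalence definition, CO-confirmed. The recall window is the sponsor's choice.
- **24-hour abstinence at month 12:** report as supportive.
- **Alternative:** if the sponsor prefers 24-hour point prevalence as primary, amend the Definitions section to say so and describe the result in those terms.
- **Planning rates:** state which definition the 9% and 24% refer to and give power under the definition chosen.

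**Cost:** a changed question on the case record form, plus a protocol and registry amendment while the trial is recruiting. No new visit or test is needed, and the new question can be put to anyone whose month-12 visit is still ahead. Reported rates will be lower under the sustained definition, and the possible loss of power shown above should be disclosed.

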#### Blood pressure

A clinical digital sphygmomanometer will be used for serial measurement of blood pressure.

#### CVD risk assessment

The CVD risk assessment will apply the general Framingham general CVD risk profile for primary healthcare [23,24]. Calculation of the Framingham CVD risk (FMH) score requires information relating to age, sex, blood pressure, diabetes status, smoking status and BMI. The FMH score will be assessed at the baseline, 6- and 12-month visits.

#### Perceived family support

A scale measuring the perceived family support, suitable for the study site setting, was not available yet. Two sections of qualitative inquiries using in-depth interviews among smokers in the Maetha district identified the construct items and afterwards were developed into a scale to measure the smoker’s family support. The scale will be validated in a pilot study of similar population.

#### Health economic assessment

Costs for providing and receiving two intervention services will be estimated by interviewing the health and administrative personnel at MH and the PCUs, as well as the participants. The cost of providing the services includes costs relating to materials, personnel and the facility. The cost of receiving the services includes participants’ time and transportation to the facility. The cost of medical services for CVDs will also be estimated, based on information from the available literature.

#### CVD events and death

Participants will be followed up by nurse-administered, structured questionnaires at the 6- and 12-month visits, ascertaining medical history, lifestyle and health-related behaviors. During each questionnaire, participants will be asked whether they have had a CVD event referred to the community hospital; any reported CVD event will be confirmed by reviewing the NCD network medical records [25].

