### Sample size

A total of 328 participants will be randomized to have 164 in the new service arm and 164 in the routine service arm. The sample size for the randomized controlled trial was calculated to have a power of 80% and 95% confidence interval so as to show the difference in primary and secondary outcomes, and the CVD incidence between the new package arm and the routine service arm. It was calculated using the power sample size calculation of Stata version 11, based on the previous year’s smoking cessation rate at the MH (9%), and the estimated cessation rate of the evidence-based package (24%). Additionally, the calculated sample size was increased by 20% to compensate for loss to follow-up.

The sample size for the additional non-randomized arm was calculated at a ratio of 1:3 compared to the total size of the two intervention arms. The power of 90% and 95 percent confidence interval will suffice to see the difference in CVD events between ex-smokers and continuous smokers, assumed as 0.1 and 0.25. Totally the sample size is 440 participants.

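### The CVD-event question is limited to events referred to the community hospital, but the endpoint carries no such limit, so the count may fall short by an unknown amount

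*Protocol article*

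**What the plan says.** Four parts of the protocol article bear on this point.

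- **Definition.** The section on cardiovascular disease (CVD) events lists myocardial infarction, coronary insufficiency, unstable angina, both types of stroke and TIA, and ends "peripheral artery disease or heart failure will be counted as CVD events in this study". It does not mention referral or place of treatment. The CVD mortality definition is equally open: "any documented death caused by CVD during the study period".
- **Outcome.** Secondary outcome 4 is "Number of CVD events and deaths at the 12-month follow-up", again without restriction.
- **Collection.** Under CVD events and death, nurses administer structured questionnaires at the 6- and 12-month visits, "ascertaining medical history, lifestyle and health-related behaviors". In these, "participants will be asked whether they have had a CVD event referred to the community hospital". Then "any reported CVD event will be confirmed by reviewing the NCD network medical records".
- **Use.** The sample size section relies on a "difference in CVD events between ex-smokers and continuous smokers, assumed as 0.1 and 0.25", with 90% power. The analysis plan compares CVD events between the two randomized arms and across all three arms. Secondary objective 5 compares them between ex-smokers, reduced smokers and continuous smokers.

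**The concern.** The described question carries a condition that the endpoint does not. Read literally, a participant whose stroke was treated at a hospital outside the network could truthfully answer no. So could one whose TIA, peripheral artery disease or heart failure was managed without referral. The record review does not repair this, because it starts from a reported event and so cannot recover one that the question left out.

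The problem lies in the scope of the question. It would remain with full attendance and perfect recall, so it is distinct from dropout and from under-reporting. At stake are the absolute event rates, the differences between groups and the precision of the CVD comparisons. The reported figure would also describe events that followed one referral route, which is not the endpoint as defined.

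**Working it through.** **1. Passages side by side.**

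| Element | Condition on referral or place of care |
|---|---|
| Definition of CVD events | None |
| Secondary outcome 4 | None |
| Question put to participants | Referred to the community hospital |
| Confirmation | NCD network records, for reported events only |

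The events that satisfy the question are a subset of those that satisfy the definition. Any discrepancy from this source is therefore downward.

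**2. Reproducing the plan's own figure.** Inputs from the sample size section: proportions 0.10 and 0.25, 90% power, 95% confidence (taken as two-sided 5%), ratio 1:3, and a 20% increase for loss to follow-up. With 0.10 in the smaller group, r = 3 and no continuity correction:

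- p̄ = (0.10 + 3 × 0.25)/4 = 0.2125
- n₁ = {[1.96 × √((1 + 1/3) × 0.2125 × 0.7875) + 1.2816 × √(0.10 × 0.90 + 0.25 × 0.75/3)] / 0.15}²
- n₁ = [(1.96 × 0.4724 + 1.2816 × 0.3905)/0.15]² = 90.4, rounded up to 91; the larger group is 3 × 91 = 273
- With the increase: 273 × 1.2 = 327.6 and (91 + 273) × 1.2 = 436.8

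The article states 328 and 440, so both are reproduced closely. The total also fits plain ratio arithmetic, 328 + 328/3 = 437.3.

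**3. Effect of missed events (illustration).** The documents give no missed share m, so a range is assumed, equal in both groups. Observed proportions are 0.10(1 − m) and 0.25(1 − m). With 91 and 273 evaluable,

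power = Φ[(d − 1.96 × SE₀)/SE₁],

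where d is the observed difference, SE₀ the pooled standard error and SE₁ the unpooled one. At m = 0.20, d = 0.12, SE₀ = 0.04547 and SE₁ = 0.03735, so power = Φ(0.827) = 79.6%.

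| Missed | Observed proportions | Difference | Risk ratio | Power |
|---|---|---|---|---|
| 0% | 0.100 vs 0.250 | 0.150 | 2.5 | 90.2% |
| 5% | 0.095 vs 0.2375 | 0.1425 | 2.5 | 88.1% |
| 10% | 0.090 vs 0.225 | 0.135 | 2.5 | 85.6% |
| 20% | 0.080 vs 0.200 | 0.120 | 2.5 | 79.6% |
| 30% | 0.070 vs 0.175 | 0.105 | 2.5 | 72.0% |
| 50% | 0.050 vs 0.125 | 0.075 | 2.5 | 52.5% |

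**4. Sensitivity to the group assignment.** The article does not say which proportion belongs to the smaller group. With 0.25 there and the same 91 and 273, power is 91.9%, 88.7%, 84.5% and 65.7% at 0%, 10%, 20% and 50% missed. The pattern is the same and the loss somewhat smaller. That assignment gives a planned total of 408, which does not match 440.

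**The case against.** The strongest reply is that one sentence in a journal article is not the instrument. The questionnaire is not shown, and the phrase may simply describe how patients usually pass from the primary care units to the hospital. That is possible. But the article does not leave the scope of the question open; it states a scope, and that scope differs from its own definition. Nothing in it says that every event reaches the community hospital.

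Second, other routes may exist. The same questionnaires take a medical history, and Table 2 lists CVD event and CVD death at months 0, 6 and 12 without a referral condition. The follow-up section adds that "most of the secondary outcomes are feasible to measure via the routine data collection of the study site hospital network". So it is not established that the quoted question is the sole source. Equally, none of these is described as a way to find events treated elsewhere, and the routine data are those of the study network.

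Third, a reader might infer that the trial will under-count CVD events, or that the definition expressly includes events wherever they are treated. The documents support neither. The definition is silent on place of care, and an actual shortfall requires that some events bypass the referral route. Participants are regular clients of the primary care units, so the missed share could be small.

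Fourth, equal loss leaves the risk ratio unchanged, and the planned Cox regression is a relative analysis. This stands: no bias between arms has been shown, only a possible loss of precision and lower absolute rates.

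A reader might also start the power calculation from the expected number of quitters, 0.24 × 164 + 0.09 × 164 ≈ 54 against the other 386, where power is already 74% with nothing missed. That lower starting point comes from a separate matter, the number of quitters, and should not be charged to the wording of this question.

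**Conclusion.** The point holds as an inconsistency to reconcile. The question as described is narrower than the endpoint it serves, and confirmation limited to reported events cannot close the gap. The count can match the definition or fall short of it; by how much cannot be obtained from the documents.

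The power figures rest on three assumptions: an assumed missed share, equal loss in both groups, and the 1:3 evaluable sizes implied by the plan. On those terms a 10% shortfall costs about 5 percentage points of power and a 20% shortfall about 11. The primary outcome is unaffected. Severity is low to moderate: the outcome is secondary, but the plan cites its event rates in justifying the sample size.

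**What to change.** Bring the data-collection section into line with the definition and the secondary outcome:

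- Delete the referral condition. At months 6 and 12, ask about any event on the protocol's list, diagnosed or treated at any facility, and record the facility and date.
- Confirm each report from NCD network records or, where obtainable, from the records of the treating facility.
- Report events that cannot be confirmed separately, as unconfirmed.

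If the questionnaire in use already asks this, correcting the description is enough. The cost is one reworded item at existing visits and a few record requests to outside hospitals, with some events left unconfirmed. No arm, visit or sample size changes. The trial is recruiting, so the change is best made before further month-6 questionnaires are completed.
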